### Composition of the data monitoring committee, its role and reporting structure {21a}

No additional monitoring committee is considered for this study. The leading investigators ([name] and [name]) will meet weekly with all the researchers involved in this study to discuss the research progress and any adverse event that arises during the procedures. Researchers are instructed to report any issue to the leading investigators immediately, who will then inform the board review committee from the San Juan de Dios, Curicó’s Hospital, and the Ethics Committee of the Universidad Católica del Maule, Talca, Chile, when appropriate.

### Adverse event reporting and harms {22}

In the end of each training session and evaluations, participants will be asked to report any complains and symptoms produced by the proposed activity. The outcome assessor and the lead researcher will be in charge to collect and record this information throughout the study. All complications and dropouts will be reported in the final manuscript.

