### Intervention description {11a}

Participants allocated to the MICT and HIIT groups will perform two weekly sessions of supervised exercise for 16 weeks. Sessions will be divided into a 3-week adaptation period and 13 weeks of formal training. All sessions will consist of:
Joint mobility (3 min): head and neck, shoulder, elbow, wrist, hip, knee, ankle, and trunk.Warm-up (7 min): treadmill walking at 1–2 km/h.Aerobic component:
MICT group: 15 min on a cycle ergometer at moderate intensity (40–60% of heart rate reserve) or at a perceived exertion rating of 5–6 out of 10.HIIT group: 8 min on a cycle ergometer, including a 60-s sprint at 90% maximal heart rate followed by a 60-s rest until four sets are completed.Strength training: 15 min of exercise in the large muscle groups with weight machines or dumbbells, including 1–2 sets of 8–10 repetitions at 50–60% of one-repetition maximum strength (1RM).Cool-down (5 min): proprioceptive neuromuscular facilitation exercises for abdominal muscles and the pelvic floor will be performed on a mat. Stretching exercises for arm, leg, and trunk muscles will be performed in three 30-s sets. Hemodynamic variables will be checked to ensure that blood pressure and heart rate values return to baseline.

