#### Exercise progression

Beginning with the fourth week, the aerobic load in the MICT group will be adjusted to 60% of the heart rate reserve and the duration will be adjusted to 30 min. In the HIIT group, the number of sets will be increased to 1 by week until 10 sprints. Strengthening exercises will be performed in 3 sets of 10–12 repetitions, with intensities between 60 and 70% 1RM. The 1RM value will be assessed at baseline and week 8.

During both training programs, heart rate, blood pressure, oxygen saturation, and perceived exertion will be evaluated with the Borg CR-10 scale.

Participants allocated to the CG will be following the indications of regular physical activity practice according to WHO (at least 150 min per week of moderate physical activity or at least 75 min of intense physical activity), which will be explained by [name]. The protocol followed by all patients operated of bariatric surgery at the San Juan de Dios hospital is to receive these indications.

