### Outcomes {12}

Outcomes will be assessed at four time points: (1) 1 week before surgery, (2) 21 days after surgery (baseline before starting the exercise program), (3) 8 weeks after the beginning of the exercise program, and (4) 1 week after the end of intervention.

Primary outcomes will be (1) body composition, (2) heart rate variability, (3) 6-min walk test results, and (4) perceived quality of life. Secondary outcomes include the results for (1) maximal respiratory pressure, (2) flowmeter, (3) hand dynamometry, (4) the 30-s sit-to-stand test, and (5) the basal metabolic rate.

Data collection will include sex, age, place of residence, marital status, education level, and physical activity level according to the International Physical Activity Questionnaire [29].

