## Assignment of interventions: allocation

### Sequence generation {16a}

#### Concealment mechanism {16b}

##### Implementation {16c}

After baseline assessment, randomization will be performed using sealed opaque envelopes. Envelopes will contain a piece of paper containing the letters A, B, or C, corresponding to the three groups of the current study. An independent researcher (i.e., not involved in the current study) will organize the envelopes in numerical order and will keep them in a safe place until baseline assessments are concluded. Then, the envelope labeled with the same number as assigned to the participants when they were included in the study will be unsealed and informed to the leading research. Participants could be assigned to one of the three groups: (1) control group, (2) moderate-intensity continuous training group, and (3) high-intensity interval training group. Figure 2 shows the study design flow chart describing all the steps of the study (Fig. 2).

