### Plans to promote participant retention and complete follow-up {18b}

A weekly phone call will be made to CG participants, asking about their health status and the indications for this group will be reinforced, in turn a text message will be sent to remind the evaluation date and time.

Participants who are in the training groups, in each session will be asked for feedback on their health status and will be sent a text message to remind them the training schedule.

In the event that any participant misses their training or evaluation, they will immediately proceed to call to ask about the reasons for not showing up.

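### The harms question is tied to training sessions that controls do not have, and the weekly control call is not named as a source of harms data, so ascertainment differs by arm

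*Protocol article*

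**What the plan says.** Adverse event reporting and harms {22} in the protocol article sets the collection rule: "In the end of each training session and evaluations, participants will be asked to report any complains and symptoms produced by the proposed activity". That section also promises that "All complications and dropouts will be reported in the final manuscript".

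Who has training sessions is settled elsewhere. Under Intervention description {11a}, "Participants allocated to the MICT and HIIT groups will perform two weekly sessions of supervised exercise for 16 weeks". Controls have none; under Exercise progression, "Participants allocated to the CG will be following the indications of regular physical activity practice according to WHO".

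Under Plans to promote participant retention and complete follow-up {18b} there is further contact between evaluations. For controls, "A weekly phone call will be made to CG participants, asking about their health status". Participants in the training groups "in each session will be asked for feedback on their health status". The harms section does not mention the call.

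**The concern.** The plan states a rule for collecting harms, and the rule follows the training timetable. An arm without training is asked the harms question only when it comes for evaluation. The wording adds to this. A question about symptoms caused by the activity has a clear meaning after a supervised cycling session and little meaning for someone who was only given advice.

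The report will present complications in three arms, and readers will set them side by side. A mild complaint that fades within days has many chances to be recorded in the exercise arms and few in the control arm. Exercise, including HIIT, could then look less well tolerated than it is. The Discussion presents the trial as a possible starting point for recommendations on supervised exercise, so apparent tolerability matters. A complaint not recorded when it occurs cannot be reliably recovered later.

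**Working it through.** The protocol prints no number of harms prompts, so there is no figure of its own to reproduce. The counts below are derived from its schedule.

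**Inputs**
- Sessions per exercise participant: 2 per week × 16 weeks = 32 (Intervention description {11a}).
- Sessions per control: 0 (Exercise progression).
- Evaluations after randomisation: 2. Under Implementation {16c}, "After baseline assessment, randomization will be performed using sealed opaque envelopes", which leaves the last two in Outcomes {12}: "3) 8 weeks after the beginning of the exercise program, and (4) 1 week after the end of intervention".
- Weekly control calls: about 16. This assumes that they run for the length of the training; the protocol gives no number.
- Follow-up from the start of training to the final evaluation: 16 + 1 = 17 weeks.

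**Prompts per participant after randomisation**
- Exercise arms: 32 + 2 = 34.
- Exercise arms at the 85% attendance floor: 0.85 × 32 = 27.2, so at least 28 sessions, and 28 + 2 = 30.
- Controls under the harms section alone: 2. The ratio is 34 / 2 = 17.
- Controls if call answers are also recorded as harms: 16 + 2 = 18. The ratio is 34 / 18 = 1.9.

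**What this could do to recorded complaints**

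This is an illustration, because the documents give no recall period. Assume that a complaint is recorded only if it arises within *w* weeks before a prompt, and that true rates are equal in all arms. For *w* of 1 week or more, sessions plus the final evaluation cover the whole period in the exercise arms. Control coverage without the calls is 2*w* / 17, and the apparent exercise-to-control ratio is its inverse.

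| Recall | Control coverage, calls not logged | Apparent ratio, calls not logged | Apparent ratio, calls logged |
|---|---|---|---|
| 1 week | 2/17 = 12% | 17/2 = 8.5 | about 1 |
| 2 weeks | 4/17 = 24% | 17/4 = 4.3 | about 1 |
| 4 weeks | 8/17 = 47% | 17/8 = 2.1 | about 1 |

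In the last column, weekly calls followed by the final evaluation leave no gap once recall reaches 7 days.

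A shorter recall gives larger ratios. With 3 days, the chance of capture is about 3/3.5 = 0.86 at twice-weekly sessions, 3/7 = 0.43 at weekly calls and 3/56 = 0.05 at evaluations 8 weeks apart. Even with calls logged, the ratio is then 0.86 / 0.43 = 2. Without them it is (3/3.5) / (3/56) = 16.

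Recall and the logging of calls therefore decide the size. The protocol leaves the second open.

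**The case against.** The strongest reply is that controls are not left alone between evaluations. They are telephoned every week about their health, and nothing says that the answers are thrown away. A condensed article would commonly leave call logs and forms to a fuller document. This stands against any claim that controls are never asked. It does not remove the point, because the article does state a rule for collecting harms, and that rule names sessions and evaluations only. The retention section gives exercise participants a health-status question as well, so the harms question appears to be something separate.

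Second, serious events have other routes. Under Composition of the data monitoring committee {21a}, staff must bring any problem to the leading investigators at once. Under Frequency and plans for auditing trial conduct {23}, the hospital board receives a monthly report that covers adverse events. Neither is limited by arm. BAROS, applied at the final evaluation, scores complications and reoperation with no arm excluded. This stands, and it confines the concern mainly to minor or transient complaints.

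Third, asking about session-related symptoms after a session is ordinary tolerability monitoring, and symptoms caused by sessions cannot occur at equal rates in an arm without sessions. This also stands. The equal-rates illustration applies to complaints that could arise in any arm, such as fatigue or pain after surgery. It is also a reason to keep session-elicited symptoms apart from events collected alike in all arms.

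Fourth, no between-arm comparison of harms is planned. Harms are not among the primary or secondary outcomes, the statistical methods address only those outcomes, and no additional analyses are planned. A reader might infer that a planned safety test is biased or that the safety conclusion will be wrong. The documents do not support that, because they promise reporting and no test.

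**Conclusion.** The point holds in a limited form. As written, the harms section gives about 34 prompts per exercise participant against 2 per control, with a question that fits controls poorly. It does not name the weekly control call as a source. Ascertainment is therefore unequal by arm in frequency, mode and wording, and this could distort a descriptive side-by-side reading of minor or transient complaints.

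The effect on recorded complaints is uncertain. For recall of a week or more, the apparent ratio runs from about 1 (calls logged) to about 8.5 (calls not logged, 1-week recall). This rests on an assumed recall window, equal true rates and about 16 calls. A reader might infer that the exercise arms will certainly appear several times worse. That follows only if call answers never reach the harms record and complaints are soon forgotten. The protocol establishes neither.

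A reader might also infer that the unequal record feeds the BAROS complications item and so a primary outcome. The protocol does not say where that item's information comes from, so this cannot be claimed.

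The change is worth making because it is cheap and the contact already exists.

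**What to change.** Amend Adverse event reporting and harms {22} as follows:

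1. Name the weekly control call as a source of harms data, entered on the same form as in the exercise arms.
2. Ask one identical question once a week in all three arms, covering any health problem since the last contact of this kind, whatever its cause. Ask it at one session per week in the exercise arms and during the call in controls. Where an exercise participant misses that session, the call already planned after a missed session can carry it.
3. Ask the same question at both evaluations after randomisation. Each arm then has 16 + 2 = 18 common prompts.
4. Base any between-arm presentation of complaints on these common prompts.
5. List complaints elicited after sessions separately, for the exercise arms only, and label them as such.

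No new routine contacts are needed. The cost is form wording, slightly more data entry and the approvals that the protocol requires for an amendment. A difference in mode remains, in person against telephone, and the report should say so. The article describes the trial as recruiting, so the report should also state which participants were followed under the present rule.

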#### Six-minute walk test

The 6-min walk test will be used to evaluate functional capacity. It will take place in a flat corridor with a 15-m track. A cone will be placed at each meter to determine the beginning and ending distance. Participants will be instructed to walk back and forth as quickly as possible for 6 min, and the total distance covered during will be recorded. Before and after the test, blood pressure, heart rate, and oxygen saturation values will be measured. Verbal encouragement will be given every minute, according to Mexican National Institute of Respiratory Disease guidelines [34].

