## Assignment of interventions: blinding

### Who will be blinded {17a}

This will be a single-blinded study where the outcome assessor (i.e., the researcher in charge of the evaluations) will have no information about the participants study group.

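### As worded, the harms section makes the blinded outcome assessor jointly responsible for complaint records that only exercise-arm participants generate

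*Protocol article*

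**What the plan says.** Blinding, section {17a}: the trial is single-blind. The outcome assessor, defined there as the researcher who runs the evaluations, "will have no information about the participants study group". Section {17b} rules out unblinding. Section {18a} gives all assessments to this one role, a physical therapist.

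Harms, section {22}, on timing: "In the end of each training session and evaluations, participants will be asked to report any complains and symptoms produced by the proposed activity". A second sentence assigns the work: "The outcome assessor and the lead researcher will be in charge to collect and record this information throughout the study".

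Who has sessions, section {11a}: "Participants allocated to the MICT and HIIT groups will perform two weekly sessions of supervised exercise for 16 weeks". Controls have none. Under Exercise progression, "Participants allocated to the CG will be following the indications of regular physical activity practice according to WHO".

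Meetings, sections {5d} and {21a}: all researchers meet weekly, and adverse events are on the agenda. No exception is made for the assessor.

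Outcome procedure, Six-minute walk test: "Verbal encouragement will be given every minute".

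**The concern.** A complaint recorded after a training session can come only from someone who trains. If the person who is meant not to know the allocation collects or files these records, that person learns who is in an exercise arm.

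The article blinds no one else, so nothing stands behind this protection. The direction of any influence is also declared in advance. The Objectives state the hypothesis that both exercise programmes will do better than standard recommendations, and that HIIT will do better than MICT. An assessor who knows that a participant is exercising, and who encourages a walk test or instructs a maximal-effort test, can shift the result towards that hypothesis without intending to.

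**Working it through.** The point rests on comparing sections, not on a figure in the plan. The sample size of 17 per group does reproduce (two-sided 5% t-test, effect size 1.01, 80% power: 16.41, rounded up to 17) and is not affected.

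**Step 1. Does the task reach the blinded role?** Section {22} names two occasions (training sessions and evaluations) and two collectors (the assessor and the lead researcher). It puts both collectors in charge of the whole of the information, for the whole study. It does not say that the assessor covers evaluations only, or that the session of origin is hidden.

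**Step 2. What does a session record reveal?** Sessions exist in MICT and HIIT and not in the control group. A record therefore separates exercise from control with certainty. It separates HIIT from MICT only if the complaint describes the exercise or the assessor attends the sessions, and the article states neither.

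**Step 3. How many participants and contacts?**
- Exercise arms: 2 × 25 = 50 of 75 participants.
- Sessions per participant: 2 per week × 16 weeks = 32 at most, of which 2 × 8 = 16 fall before the 8-week assessment.

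**Step 4. Which assessments are exposed?** Randomization follows the baseline assessment (section {16c}). Of the four assessment points, the pre-surgery and 21-day ones precede allocation. The 8-week and final ones are exposed.

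**Step 5. Which outcomes are exposed?**
- More exposed: the 6-minute walk (primary, with encouragement) and the secondary tests that depend on effort (respiratory pressures, peak flow, handgrip, sit-to-stand).
- Less exposed: bioimpedance, recorded R-R intervals and the participant-scored Moorehead-Ardelt questionnaire.

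**Step 6. Is there a second route?** Section {17a} calls the assessor a researcher. Sections {5d} and {21a} bring all researchers together weekly, with adverse events discussed. An event described as arising in a session carries the same information as the record.

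**Step 7. What could it do to an exercise-versus-control comparison?** The documents give no bias. For illustration only, assume no true effect and a shift of b standard deviations, in a simple two-group comparison at two-sided 5% without Bonferroni correction. With SE = √(2/n), the false-positive rate is 1 − Φ(1.96 − b/SE) + Φ(−1.96 − b/SE).

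| Assumed b (SD) | n = 25 per group | n = 17 per group |
|---|---|---|
| 0.1 | 6% | 6% |
| 0.2 | 11% | 9% |
| 0.3 | 19% | 14% |
| 0.5 | 42% | 31% |

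For n = 25 and b = 0.2: SE = √(2/25) = 0.283, b/SE = 0.707, and the rate is 0.109. The table shows sensitivity to an assumption and does not estimate the bias in this trial.

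**The case against.** The strongest reply is that the sections can be reconciled. Two occasions and two collectors suggest a natural split: the lead researcher, who is told the allocation under section {16c}, takes the sessions, and the assessor, whose role is the evaluations, takes the evaluations. On that reading blinding survives, and a condensed article may simply have left the split to the full protocol. This reply stands in part. It means that a reader should not infer that the two sections are impossible to follow together, or that blinding is certain to be lost. It does not remove the point, because the printed sentence assigns everything to both roles and no other section limits it.

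A reader might also infer that the assessor will tell HIIT from MICT and favour HIIT. The article does not support this. It does not say that the exercise type is recorded with the complaint. Knowledge of exercise versus control alone would affect both exercise arms alike and would not in itself bias the comparison between them.

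A third tempting inference is that all the primary outcomes are compromised. Of the four, only the 6-minute walk depends clearly on how staff encourage the participant, and the timing of that encouragement is fixed at every minute under a cited guideline. That limits the latitude, though it does not fix tone or intensity. For the other effort tests the article describes instruction and not encouragement, and all of them are secondary.

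**Conclusion.** The point holds as a conflict in the wording that needs to be resolved. As printed, the harms section gives the blinded assessor joint responsibility for records that identify exercise-arm participants, contrary to sections {17a} and {17b}. The weekly meetings add a second route.

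If the assessor does handle session complaints, allocation to exercise or control becomes visible for up to 50 of 75 participants before the 8-week and final assessments. The 6-minute walk and the effort-dependent secondary tests would then be open to detection bias in the direction of the stated hypothesis. If the lead researcher alone covers sessions, that route is closed and only the meetings remain.

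The conclusion assumes that section {22} is applied as written and that the assessor attends the researchers' meetings. The size of any bias cannot be derived from the documents.

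**What to change.** - Amend section {22} so that complaints from training sessions are recorded only by the physiotherapists supervising the sessions, who must not include the assessor, and by the lead researcher.
- Limit the assessor to complaints asked at evaluations, in identical words for all three arms and without reference to sessions.
- Keep the assessor away from session records, and out of the adverse-event part of the weekly meetings, until the last assessment is complete. Say so in sections {17a}, {5d} and {21a}.
- If the lead researcher was always meant to cover the sessions, one sentence saying so settles the first item. The restriction on meetings is still needed.

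The cost is an amendment and a change of duties among existing staff. The article lists the trial as recruiting, so the change can protect assessments still to come. The report should give the date of the change and state whether the assessor had seen session complaints before it.

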### Frequency and plans for auditing trial conduct {23}

The trial conduct will be continuously monitored by the leading investigators. The San Juan de Dios, Curicó’s Hospital Review Board requires monthly report to get informed about the research’s progress and the occurrence of any adverse event. No extra auditing is considered for this study, unless requested by the Hospital’s Review Board or the Ethics Committee of the Universidad Católica del Maule.

